***Results of the optimisation and pilot RCT study***

Intervention optimisation involved collaboration with one secondary school, and PPI with the Advice Leading to Public Health Action (ALPHA) group of young people based at the DECIPHer Centre in Cardiff, trained to provide advice on public health research, as well as a group of policy/practice stakeholders. This elaborated Positive Choices from a basic description to a fully specified intervention with materials. This was successful and all components were successfully feasibility-tested in the collaborating school. The curriculum was refined and broadened from that originally planned to ensure that it provided comprehensive RSE while still addressing all topics in the protocol. Social-marketing campaigns segmented student audiences only on age, informed by PPI with teachers and students suggesting that other targeting would stigmatise those students. Review of sexual and reproductive health services was reoriented away from what was originally planned as SEF consultancy for schools, towards a guided school self-audit to increase cost-efficiency and school capacity for sustainability.

In the subsequent pilot RCT across 6 schools, all criteria for progression to phase III were met. All schools were randomised, 4 to intervention and 2 to control, and remained in the study. Student response rates in intervention and control groups were 89% and 84% at baseline, and 89% and 82% at follow-up. The intervention was implemented with fidelity in 3 intervention schools with limited data from 1 school preventing assessment of fidelity. Around two-thirds of students reported awareness of the intervention, and around 80% of these students and all staff interviewed indicated acceptability. Positive Choices students reported significantly more comprehensive coverage of RSE topics than controls. Linkage of self-report and registered births and terminations was feasible but, unsurprisingly given students’ ages and national trends, there were no registered births or terminations among trial participants.

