1. What is the effect of the Positive Choices intervention in intention-to-treat analyses on student-reported measures of non-competent first sex (primary outcome), and various pre-hypothesised secondary outcomes and intermediate outcomes?

2. Where plausible, are these associations moderated by student gender, sexual orientation, ethnicity or socio-economic status (SES), or by school-level GCSE attainment or local deprivation?

3. Are associations greater in on-treatment analyses accounting for intervention fidelity?

4. What does the intervention cost and is it cost-effective?

5. Is the intervention delivered with good fidelity, reach and acceptability and how does this vary between schools and students?

6. What is usual treatment in control schools?

7. What do qualitative data suggest about implementation processes/intervention mechanisms and how these might vary between schools or students?

8. What do the trial findings overall suggest about the intervention theory of change and the potential for the intervention to be delivered and be effective elsewhere?

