**Methods**

***Design***

We will conduct a superiority, phase-III cluster parallel-group RCT to assess whether incorporating Positive Choices into school provision is more effective than usual provision (see figure 1). The trial will comprise 50 schools (minimum 6440, maximum 8500 students) allocated 1:1 to intervention/control assessing primary and secondary outcomes at 33 months using primary intention-to-treat analyses, and using realist approaches to assessing contextual variations in implementation, mechanisms and outcomes.

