***Analytic sample and sample size***

We calculate that, for 80% power with 5% significance, conservatively assuming: a sample of 140 students per school; drop out of 2 schools per arm; 80% student survey response rate at follow-up; an intra-cluster correlation coefficient (ICC) of 0.015 for our primary outcome; and prevalence of this outcome of 9% among those in the control arm, we will require 25 schools per arm to detect a 36% reduction in the primary outcome (giving a prevalence of 5.85% in the intervention arm). The minimum analytic sample for outcome assessment in the RCT will therefore be approximately 6440 students providing follow-up data at 33 months. Repeating this power calculation for the originally intended primary outcome of conceptions (where the prevalence among female controls would be around 2%)(13) would require >100 schools per arm.

These estimates are informed by research and PPI. We assume 140 students per school informed by our recent INCLUSIVE trial.(52) This is a conservative assumption for the Positive Choices trial because the average year group has now risen to 190 and so assuming an 80% response rate (again informed by the Positive Choices pilot and previous studies(42, 52-54)) this would comfortably provide over 150 students.(55) Two schools dropping out is also a conservative assumption given our previous trials have experienced no drop outs.(42, 52, 53) Regarding ICCs, no data are available on school-level clustering of lack of sexual competence at first sex but we would expect this to be very similar to ICCs for non-use of contraception at first sex, which are reported as 0.01(56, 57) so a conservative assumption of 0.015 for this study is reasonable.

Our assumption about prevalence of the primary outcome among controls is also informed by the literature. Around 25% of 15-16 year-olds are sexually active compared with 7% of 12-13 year-olds.(58) Therefore, between baseline and follow-up, we would expect 18% of students to become sexually active. Data from young people participating in the third Natsal sexual behaviour survey suggest that, among those aged 15-16 years, around half lack sexual competence at first sex.(1, 2) Therefore, we would expect around half of trial participants who become sexually active by follow-up (i.e. 9% of all participants) will experience non-competent sexual debut.

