A statistical analysis plan will be drafted by the CTU and a data dictionary by the fieldwork team. Statistical analysis of survey data will be led by the CTU, with analysis of fidelity data by the fieldwork team and economic data by [name]. School randomisation and retention, and student response rates will be described using a CONSORT diagram.(88) Baseline and follow-up data will be tabulated by arm. Continuous outcomes will be summarised for each trial arm using means and standard deviations and binary outcomes will be summarised for each trial arm using numbers and percentages. We will conduct intention-to-treat analyses of primary and secondary outcomes (88) as well as exploratory analyses of our intermediate outcomes (RQ1) to estimate intervention effects, reporting 95% confidence intervals and P values for primary and secondary outcomes but not for exploratory analyses of the intermediate outcome. The analytic sample will be students providing follow-up data at 33 months. Analyses will account for school clustering. All outcomes will be analysed using generalised estimating questions (GEEs) with an exchangeable correlation structure and the sandwich estimator of variance to adjust for clustering, with small sample bias correction for the degrees of freedom. For binary outcomes GEEs will be fitted, with a log link to estimate risk ratios and identity link to obtain risk differences. In the event of low prevalence resulting in non-convergence of the GEE model a hierarchical modified Poisson regression model will be used to obtain risk ratios, followed by marginal standardisation to obtain risks for calculating risk differences where required. For continuous outcomes GEEs with an identity link will be used to obtain mean differences.

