The primary analysis of all outcomes will include adjustment for stratification factors used in the randomisation. Our primary analysis will be an analysis that is adjusted for the stratification factors only. An additional adjusted analysis will be carried out which will adjust for prespecified cluster level summaries of baseline student age, gender, ethnicity and SES (as measured by the family affluence scale), imputed where feasible from baseline data if missing at follow-up. In addition, any other major imbalances observed between randomised groups will be adjusted for in exploratory secondary analyses. Interim analyses will not be conducted and will not inform intervention modification or discontinuation because this is a cluster RCT with one follow-up wave.

We will undertake exploratory tests of interaction to assess how effects are moderated, including by student gender, sexual orientation, ethnicity and SES as well as by school GCSE attainment and local deprivation (RQ2). These will be exploratory, with limited statistical power. We will also undertake complier-average causal effects analyses to examine how effects are affected by fidelity of implementation (RQ3). Economic analyses will calculate intervention costs and cost-effectiveness (RQ4) (see below). Descriptive statistics will describe fidelity, reach and acceptability using Chi-square tests to examine differences between schools. These will examine whether fidelity differs by school-level GCSE attainment and local deprivation, and whether student-level reach and acceptability differ by student-level gender, sexual orientation, ethnicity and SES. (RQ5). Quantitative and qualitative data from control schools will be analysed to describe usual treatment in control schools (RQ6). Qualitative data will also be used to develop hypotheses about implementation processes/intervention mechanisms and how these might vary between schools or students (RQ7). We will draw on all data to refine the intervention theory of change and draw conclusions about the potential for the intervention to be delivered and be effective elsewhere (RQ8).

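### Under its standard assumptions, the complier-average analysis assigned to RQ3 can only match or exceed the ITT effect in size, so finding it greater is not evidence that fidelity matters

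*Combined protocol and SAP*

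**What the plan says.** The third research question, under Rationale and aims, is comparative: "Are associations greater in on-treatment analyses accounting for intervention fidelity"? Under Data management and analysis, the method given for it is "complier-average causal effects analyses to examine how effects are affected by fidelity of implementation (RQ3"). The protocol does not say who counts as a complier (school or student, which components, what cut-off), which estimator will be used, or which assumptions it rests on.

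The same section fits the binary outcome models "with a log link to estimate risk ratios and identity link to obtain risk differences", so both scales matter here.

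Under Process evaluation data collection, fidelity is to be measured quantitatively for every component. Under RQ5 that measure is only described and compared between types of school. The later exploratory work on mediation and moderation does not name fidelity. No analysis of outcome against a graded fidelity score is planned. RQ8 then draws on all the data to refine the theory of change and to judge whether the intervention could work elsewhere.

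On likely compliance, the protocol offers only the pilot: "The intervention was implemented with fidelity in 3 intervention schools with limited data from 1 school preventing assessment of fidelity".

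**The concern.** The question and the method do not fit. A reader of RQ3 expects the comparison with the ITT to show whether better delivery goes with a larger effect. The standard complier-average estimator cannot show that. It rescales the ITT by the compliant share, and it assumes that schools below the cut-off gained nothing. The link between fidelity and effect is therefore an assumption of the method and is not tested.

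That assumption is doubtful for this package. Positive Choices combines 16 lessons over two years (8 + 5 core, 2 + 1 add-on), a council that meets each term, a yearly student campaign, materials for parents and a review of services. A school can fall short of a cut-off and still deliver much of it.

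At stake is the answer to RQ3 and its use in RQ8. A larger complier effect could be taken as support for the theory of change when it follows from the arithmetic alone.

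**Working it through.** **Inputs.** The planned effect, 9% against 5.85%, comes from Analytic sample and sample size and gives an ITT risk difference of −3.15 points. The compliant share p is not given for this trial. In the pilot, 3 of 4 intervention schools had fidelity and 1 could not be assessed, so p lies between 3/4 = 0.75 and 1. I also show values down to 0.5 as an assumption. Control access is taken as none: Intervention and comparator reports that pilot schools offered nothing equivalent, although contamination will be examined.

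**1. The plan's own figure.** The plan assumes "a sample of 140 students per school" and "drop out of 2 schools per arm" from 25. This gives 2 × 23 × 140 = 6440, as stated. The design effect is 1 + 139 × 0.015 = 3.085, and the effective number per arm is 3220 / 3.085 = 1043.8. Power at two-sided 5% (sidedness assumed) is 78.4%, within 2 points of the stated 80%. The −3.15 points is therefore a fair effect to carry forward. The plan has no complier figure to reproduce.

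**2. Risk difference.** With C the effect in compliers and N the effect below the threshold,

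ITT = p × C + (1 − p) × N.

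Setting N = 0 (the exclusion restriction) gives C = ITT / p.

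| p | C when ITT = −3.15 | Factor 1/p |
|---|---|---|
| 1 | −3.15 | 1.00 |
| 0.9 | −3.50 | 1.11 |
| 0.75 | −4.20 | 1.33 |
| 0.6 | −5.25 | 1.67 |
| 0.5 | −6.30 | 2.00 |

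An ITT of 0 gives 0. A harmful ITT of +1.0 point gives +1.33 at p = 0.75. If p is treated as known, the standard error is also divided by p, so the test statistic does not change.

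**3. Risk ratio.** Let c be the control-arm risk among would-be compliers. The complier ratio minus 1 is ITT / (p × c); the ITT ratio minus 1 is ITT / 9%. Since p × c cannot exceed 9%, the complier ratio is at least as far from 1. The ITT ratio is 5.85 / 9 = 0.65. At p = 0.75 the complier ratio is (6 − 4.2) / 6 = 0.30 at c = 6%, (9 − 4.2) / 9 = 0.53 at c = 9%, and (12 − 4.2) / 12 = 0.65 at c = 12%, the highest feasible value (0.75 × 12 = 9).

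**4. Does the estimate track fidelity?** A simulated fidelity score (Beta(3,2), mean 0.6, threshold 0.6, about 52.5% compliers) was combined with three true patterns, each with an ITT of about −3.15 points.

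| True pattern | Effect in compliers | Effect below threshold | Complier estimate |
|---|---|---|---|
| Flat | −3.15 | −3.15 | about −6.0 |
| Rises with fidelity | −3.98 | −2.24 | about −6.0 |
| Falls with fidelity | −1.91 | −4.52 | about −6.0 |

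By hand, −3.15 / 0.525 = −6.0. The estimate is the same in all three.

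**5. Partial delivery.** Let compliers have effect E and the rest half of it. If 75% comply, ITT = 0.75E + 0.25 × 0.5E = 0.875E, and 0.875E / 0.75 = 1.17E, which is 17% too large. If 50% comply, ITT = 0.75E, and 0.75E / 0.5 = 1.5E, which is 50% too large. The half-effect and the 50% share are illustrations only.

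**6. A graded score.** With allocation as the only instrument and the score set to 0 in controls, the estimate is the ITT divided by the mean score. In step 4 that is −3.15 / 0.6 = −5.25 for all three patterns. In the first case of step 5, if the remaining schools score 0.5, the mean score is 0.75 + 0.25 × 0.5 = 0.875, and 0.875E / 0.875 recovers E.

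**The case against.** The strongest reply is that the protocol names a family of methods and fixes none of the assumptions used above. A model that relaxes the exclusion restriction could return a complier effect smaller than the ITT, because C falls below the ITT in size when N exceeds it. This stands, and the point is conditional for that reason. The protocol states no such model.

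The version log refers to a SAP agreed with the data monitoring and ethics committee in January 2023. Its detail on this analysis is not in the text reviewed and cannot be judged. Even so, a fully specified standard complier analysis would still not answer RQ3 as worded.

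A reader might infer that the answer to RQ3 is settled before any data are seen. That goes too far: the complier effect equals the ITT if every school complies, and it is zero if the ITT is zero. Only the ordering by size is fixed. A reader might also infer that the analysis is uninformative about delivery. It is not: the effect among those reaching a threshold is a legitimate estimand, and its size and interval carry information. What it lacks is a test of a dose gradient.

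The pilot does not establish 75% compliance. All three assessable schools had fidelity, so inflation could be nil, and the pilot curriculum covered year 9 only. Nor does any passage say that the trial will report stronger effects with better fidelity; the risk lies in how RQ3 invites the result to be read.

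**Conclusion.** The concern holds in conditional form. With no control access and no effect below the threshold, the complier effect is ITT / p. It cannot be nearer zero than the ITT, is strictly larger in size when p is below 1 and the ITT is not zero, and does not depend on how the true effect varies with fidelity. Over the pilot's range, p = 0.75 to 1, the planned −3.15 points becomes −4.20 to −3.15. Partial delivery below the threshold adds an overstatement that the documents do not allow anyone to quantify. A complier effect larger than the ITT is therefore not evidence that fidelity matters. This is a supplementary analysis: the ITT primary analysis and the sample size are untouched.

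**What to change.** - Reword RQ3 to ask what the effect is in schools that deliver the intervention as intended.
- Report the complier effect as an estimand in its own right, with the estimator, the exclusion restriction and the no-access assumption stated.
- State that a complier effect larger than the ITT will not be read as evidence that fidelity increases the effect, and will not be used that way for RQ8.
- Fix the complier definition (unit, components and cut-off) before outcome data are seen. Supplementary material 4 already reports endline response, so the date of that decision, and whether outcomes by arm had been seen, should be recorded.
- Optionally add a graded-fidelity instrumental-variable estimate, only as an exploratory sensitivity analysis for partial delivery. It should not replace the complier analysis as an answer to the original question: it assumes a linear dose effect, also rescales the ITT by construction, and does not test a gradient.

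The cost is wording in the protocol and SAP and, if the option is taken, one further model with a graded score built from the fidelity measures already planned. The downside is a more modest claim about fidelity.

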***Process evaluation data collection***

Integral process evaluation informed by existing frameworks(82-85) will examine: intervention fidelity, reach and acceptability and how this varies by school and student; usual treatment in control schools and potential contamination; and implementation processes/intervention mechanisms and how these vary between schools and students.

***Intervention fidelity, reach, acceptability and context:*** Fidelity of implementation of all intervention components by schools and preparatory activities (start-up meetings; training) by SEF will be assessed quantitatively using bespoke measures developed in the pilot RCT. Data will be collected via: audio-recording of SEF training for school staff; surveys of school staff trained by SEF; logbooks of school staff implementing internal training, school health promotion councils, curriculum and social marketing meetings; and structured researcher observations of one randomly selected session per school of internal training, school health promotion councils, curriculum lessons and social-marketing meetings. Across all schools, the RSE coordinator will complete one logbook summarising delivery across the school and teachers will complete one logbook summarising whether the key points of each lesson were taught. In the four case study schools (see below), logbooks will examine delivery of the contents of each lesson in more detail. This approach is informed by the finding from the pilot RCT that collecting detailed information on delivery of every lesson from every teacher is not feasible or acceptable to teachers. Observations will act as a check on the reliability of data from log-books. We will primarily assess fidelity of form (i.e. of activities) but where local adaptations are made we will assess whether these are consistent or not with intervention theory of change in order to provide a qualitative assessment of fidelity of function (i.e. to theory of change).(86) We will examine reach and acceptability to students (overall and by student gender, sexual orientation, ethnicity and SES, and by school-level GCSE attainment and local deprivation) quantitatively via questionnaire survey items at follow-up.

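### The Chi-square tests named for student-level reach and acceptability carry no adjustment for school clustering; the error is large for school-level factors and ranges from none to several-fold for student-level factors

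*Combined protocol and SAP*

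**What the plan says.** The Data management and analysis section gives the method for RQ5: "Descriptive statistics will describe fidelity, reach and acceptability using Chi-square tests to examine differences between schools". It then assigns factors to measures. On fidelity: "These will examine whether fidelity differs by school-level GCSE attainment and local deprivation". On the student measures, the tests are to show "whether student-level reach and acceptability differ by student-level gender, sexual orientation, ethnicity and SES". No adjustment for clustering is attached to any of these.

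The Process evaluation data collection section plans more. It examines students' reach and acceptability by the same four student characteristics "and by school-level GCSE attainment and local deprivation) quantitatively via questionnaire survey items at follow-up". The Equity section repeats the commitment to assess reach and acceptability by the two school-level measures. Neither section names a test.

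Earlier in Data management and analysis there is one general sentence: "Analyses will account for school clustering". It stands among the outcome analyses and is followed directly by the GEE specification for outcomes (exchangeable correlation, sandwich variance, small-sample correction).

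**The concern.** Reach and acceptability are reported by students, but the curriculum is delivered school by school by school staff, so answers within a school are likely to be correlated. An ordinary Chi-square test treats every student as independent. If the characteristic being compared is fixed for the whole school, or is unevenly spread across schools, the test understates the variance and rejects too often.

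The general clustering sentence does not settle the matter. If it covers RQ5, it sits badly with the test that is named. If it covers only the outcome models around it, RQ5 has no clustering method. Either way the text needs an edit. The same section gives the analysis of fidelity data to the fieldwork team rather than the trials unit, which is a further reason to write the process-evaluation methods out.

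At stake are the RQ5 statements about who was reached, the equity reporting, and the use of all data to judge whether the intervention could be delivered elsewhere. A spurious finding that reach differs by deprivation or attainment would feed into each.

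**Working it through.** **The plan's own figures.** The documents give no error rate for the Chi-square tests, so there is none to reproduce. The sample size, which supplies the cluster size and the only ICC, can be checked. Its inputs are "for 80% power with 5% significance", "a sample of 140 students per school", ICC 0.015, 9% against 5.85%, and "drop out of 2 schools per arm".

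- Under individual randomisation: 1,087 students per arm.
- Design effect: 1 + 139 × 0.015 = 3.085.
- Schools per arm: 1,087 × 3.085 / 140 = 23.95, or 24.9 by the unpooled formula with one cluster added; the plan has 25.
- Minimum sample: 46 × 140 = 6,440, as stated. Power with 23 schools of 140 per arm is 78.4%, close to 80%.

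**Inputs for the RQ5 check.**

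- Students per intervention school at endline: 3,122 / 22 = 141.9 (Supplementary Material 4).
- Reach prevalence for simulation: 0.667, from the pilot finding that around two-thirds of students were aware of the intervention.
- Single-sex schools: 4 girls-only and 2 boys-only of 49 (Supplementary Materials 5).
- ICC for reach or acceptability (ICC_y): not given. Assumed range 0.015 to 0.10; the lower end is borrowed from the primary outcome.
- ICC of the comparison factor (ICC_x): not given for ethnicity or SES. Assumed range 0.05 to 0.3.

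**Formula.** True size of a nominal two-sided 5% test = 2 × [1 − Φ(1.96 / √DE)]. For a school-level factor DE = 1 + (m − 1) × ICC_y. For a student-level factor DE = 1 + (m − 1) × ICC_x × ICC_y. Schools are taken as equal in size. Simulation used 22 schools of 142 students, with 4,000 runs per scenario.

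**School-level factor (m = 141.9).**

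| ICC_y | DE | 1.96/√DE | True size, formula | Simulation |
|---|---|---|---|---|
| 0.015 | 3.11 | 1.11 | 26.7% | 27.2% |
| 0.05 | 8.05 | 0.69 | 49.0% | 49.4% |
| 0.10 | 15.09 | 0.50 | 61.4% | 61.5% |

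With 112 students per school (140 × 0.8) the figure at ICC 0.015 is 23.0%.

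**Student-level factor.**

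| Factor | ICC_y 0.015 | ICC_y 0.05 | ICC_y 0.10 |
|---|---|---|---|
| Evenly mixed across schools (simulation) | 4.7% | 4.4% | 3.8% |
| Gender, 3 of 22 schools single-sex (simulation) | 9.4% | 15.6% | 26.5% |
| ICC_x 0.05 (formula) | 6.2% | 9.2% | 13.3% |
| ICC_x 0.2 (formula) | 10.0% | 20.7% | 31.6% |
| ICC_x 0.3 (formula) | 12.5% | 26.7% | 39.1% |

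Simulation of the last three rows gave slightly lower values at the extremes (5.7% and 37.4%).

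The 3 of 22 is 22 × 6/49 = 2.7, rounded; the split by arm is not reported. As a cross-check, suppose mixed schools are half girls. The proportion of girls over 49 schools is then 25.5/49 = 0.520, the between-school variance is 0.0302, and the gender ICC is 0.0302 / (0.520 × 0.480) = 0.12. The formula with that ICC gives 8.0%, 14.9% and 23.2%, in line with the simulation.

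**Fidelity.** Here the school is the unit. In a 2×2 table with 22 schools split 11/11 by attainment, and k schools in one fidelity category, the expected counts are k/2 and (22 − k)/2. All reach 5 only when k is 10, 11 or 12. The documents do not give the fidelity categories or their split.

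**The case against.** The best defence has four parts.

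First, the analysis section compares reach and acceptability by student-level characteristics, and a characteristic evenly mixed within schools produces no inflation. That stands. A reader might infer that every RQ5 P value is several times too liberal; the documents do not support this, because the section ties the school-level factors to fidelity. Applying Chi-square to reach by attainment or deprivation is an inference from the other two sections, which name no test of their own.

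Second, the quoted sentence speaks of differences between schools. If school itself is the factor tested, between-school variation is what the test looks for, and clustering does not invalidate it. That stands too.

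Third, the general clustering sentence may already cover RQ5. This is possible, but then the named test does not carry it out. A reader might call this a flat contradiction; given where the sentence stands, ambiguity is as much as can be shown.

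Fourth, no ICC for reach is given, and nothing in the documents places it at the high end. That also stands, so the results are shown from 0.015 upwards. At 0.015 the school-level figure is still about 27%, so the main case does not rest on a large assumed ICC.

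On fidelity, a reader might infer that small expected counts will be the rule. That depends on category splits that are not stated.

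**Conclusion.** The point holds in a limited form. A plain Chi-square test is named for student responses nested in schools, and nothing clearly attaches a clustering adjustment to it.

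- **Reach and acceptability by school-level attainment or deprivation:** if the same test is used, true size is about 27%, 49% and 61% at reach ICCs of 0.015, 0.05 and 0.10.
- **Gender:** about 9-26%, if about 3 of 22 intervention schools are single-sex.
- **Ethnicity or SES:** about 6-39%, for factor ICCs of 0.05 to 0.3 and reach ICCs of 0.015 to 0.10.
- **A factor evenly mixed within schools:** about 4-5%, so no inflation.

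The reach ICCs and the factor ICCs for ethnicity and SES are assumptions. RQ5 is descriptive process evaluation. The primary and secondary outcomes use clustered GEE, so a reader should not infer any effect on the effectiveness conclusions.

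**What to change.** In the RQ5 sentences of Data management and analysis:

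1. For student-level reach and acceptability by student or school characteristics, replace Chi-square with the GEE already specified for outcomes: exchangeable correlation, sandwich variance, small-sample correction. This suits every such comparison, whether or not the factor clusters.
2. List the comparisons by school-level GCSE attainment and local deprivation there, so that the section matches Process evaluation data collection and Equity.
3. For school-level fidelity, with about 22-25 schools, use exact tests where expected counts are small.

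The cost is a few sentences and a little more analysis work, using a method the team will already be running. RQ5 results will be less often significant and their intervals wider. For school-level factors the widening is about √DE: √3.11 = 1.8 times at ICC 0.015 and √15.09 = 3.9 times at ICC 0.10.
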